### Assessments

In order to compare study participants with non-participants, routine data are collected of all inpatients, who are admitted to the rehabilitation clinic during the period of recruitment (T0). These include demographic data (e. g. age, sex), diagnosis and work ability resp. level of functioning at discharge.

In further assessments, only participants of the study are included after they have given written consent. These questionnaires are given online with SoSci Survey [28] at www.soscisurvey.de and all data are assessed pseudonymous. Assessments will be conducted after discharge of inpatient rehabilitation, before the start of the online aftercare (baseline = T1), 1 week after the last writing-impulse is given (post-intervention = T14) as well as during the 12 weeks of the intervention (T2 to T13).

### T1 and T14 assessments

A subscale of the Patient Health Questionnaire (PHQ-9) [29] measures depression, the General Anxiety Disorder Scale (GAD-7) [30] assesses generalized anxiety. The Subjective Prognosis of Work Ability Scale (SPE) measures subjective prospects of work ability [31]. Participants’ ability to work will be measured with the short form of the Work Ability Index (WAI) [32]. By means of the Somatic Symptom Scale-8 (SSS-8) [33] and the EQ-5D [34] the burden of somatic factors and the overall health status will be assessed. Additionally, participants´ psychological and psychosocial stressors are measured by the Perceived Stress Scale (PSS-4) [35] and the corresponding subscale of the Patient Health Questionnaire (PHQ-stress module) [36]. The personal resources will also be assessed with the Oslo Support Scale (OSS-3) [37] and the Brief Resilient Coping Scale (BRCS) [38]. Furthermore the Sheehan-Disability Scale [39] is used to measure the general capability and the Loneliness Scale (LS-S) [40] assesses social integration. In addition to these assessments at T14 participants will be asked about their utilization and their evaluation about helpfulness and overall satisfaction of *‘GSA-Online plus’* (incl. helpfulness of the video clips). Satisfaction will be measured with a modified version (wording adapted for online-intervention) of the ZUF-8 [41]. Furthermore, participants´ willingness to pay for the attendance on *‘GSA-Online plus’* and the costs of the programme will be assessed.

### T2 to T13 assessments

In longitudinal assessments, once a week during the online aftercare (T2-T13), the participants` self-rated work ability is assessed by one item from the Work Ability Index [32] (‘Current work ability compared with the lifetime best.’) and the self-rated health status is measured by one item from the EQ-5D (“Your own health state today.”) [34], both on a Likert-Scale from 0 to 10. In addition, the evaluation of helpfulness and contentedness with the therapeutic feedback will be assessed.

### Objective

In the current trial, we focus on implementing the online aftercare intervention into routine care. Like other follow-up recommendations, referral is done by the medical staff. By adding introductory modules, we enable participants to obtain information about the programme online. The purpose of the implementation study is to examine, how the transdiagnostic aftercare *‘GSA-Online plus’* can be optimally implemented into regular care so that it can be offered to vocationally stressed patients in different areas and clinics of rehabilitation.

The issues are: (1) How many patients receive the aftercare referral of *‘GSA-Online plus’* under conditions of usual care and (2) what is the proportion of patients who follow this referral and use *‘GSA-Online plus’* at least once after inpatient rehabilitation.

Furthermore, we want to determine how different levels of utilization of the aftercare are associated with improvements of the subjective prognosis of work ability and distress. We assume that regular users have a more positive prognosis of work ability and less distress after participation compared to non-regular users, resp. drop-outs. And in an explorative analysis, we want to know how satisfied patients are with the aftercare and how much they would pay for participation.

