**Fig. 1 Fig1:**
[figure not shown]
Overview of the course of the trial

The current study is a single group assignment with an anticipated sample size of *N* = 212 participants. We perform a combined cross-sectional and longitudinal assessment. Based on clinic routine documentation all patients admitted during the recruitment period are documented. All patients who obtain an aftercare recommendation of *‘GSA-Online plus’* and give written consent to take part in the study are followed longitudinally.

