### Participants and recruitment

Recruitment is performed in three rehabilitation clinics specialized for psychosomatic, oncological, orthopaedic and rheumatic as well as cardiological diseases, which had not been involved in the previous trial. Physicians in charge received written information material about *‘GSA-online plus’* and were instructed about the inclusion criteria before recruitment started, however no formal screening of patients is involved. Patients are eligible if they a) are employed and return to their workplace within 4 weeks after inpatient medical rehabilitation, b) are able to write in German language, c) are between 18 and 59 years old and d) have a private internet access. The presence of comorbid mental disorders is not an exclusion criterion. A severe physical or mental disorder requiring an intensive treatment after rehabilitation precludes recommendation of online aftercare. Physicians are suggested to recommend the programme if indicated, according to their judgement (e.g. anticipated problems in vocational reintegration). This decision does not affect referrals for other aftercare programmes. In any case the physician responsible documents referrals for *‘GSA-Online plus’* or other aftercare recommendations and the agreement or refusal of the patient.

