### Statistical analysis

Frequencies and descriptive statistics will be used to evaluate recommendation rate and utilization of *‘GSA-Online plus’*. The differential efficiency of subjective prognosis of gainful employment and depression will be analysed with repeated measures ANOVA and regression analysis. Willingness to pay and the utilization criteria of online aftercare will be reported with frequencies and descriptive statistics.

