## Discussion

While internet-based interventions have been demonstrated to be efficacious, drawbacks refer to participation and implementation into clinical practice. In clinical practice, participation rates and compliance have been found to be less than satisfactory [42]. Thus, most programmes have not found a place in usual care. Dissemination and implementation of efficacious, evidence-based treatments into medical practice has become a growing issue for mental health care [43]. Therefore it is important to investigate how interventions evaluated in RCTs with selected participants, usually recruited over the internet, can be transferred into routine clinical care, and whether the health care system benefits from such developments. Thus, we implemented a transdiagnostic programme found efficacious in a previous RCT [25] into clinical practice. However, in order to be successfully implemented in routine clinical care, an online intervention needs to be self-explanatory, i.e. easy to handle by busy and changing staff members. Therefore, we augmented the programme by additional exploratory and motivational videos on the study web application to familiarize potential participants and medical professionals with the internet-based aftercare programme. Based on our previous experience with a considerable number of drop-outs from the programme we also took care to motivate them to follow through with it [26]. As other aftercare interventions, referrals to *‘GSA-Online plus’* are made by the physicians in charge. The focus of evaluation is on acceptance of the programme, both by the physicians in charge and the patients. The lack of a control group may be seen as a limitation. However, we take care to specify who gets referred, respectively accepts the recommendation compared to those who do not get the recommendation, respectively refuse to participate. Additionally, we assess the frequency and subjective evaluation of participation in order to model treatment gains based on regular participation. If our implementation study proves to be successful, a next step will be to resolve legal requirements and financial resources necessary to implement *‘GSA-Online plus’* as a regular aftercare programme for vocationally stressed inpatients of medical rehabilitation.

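### In a single-group study, the contrast between self-selected regular and non-regular users is presented as modelling treatment gains, although it can show only an association

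*Protocol article*

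**What the plan says.** - **Study design:** "The current study is a single group assignment with an anticipated sample size of" 212. There is no comparator.
- **Objective:** the aim is to learn "how different levels of utilization of the aftercare are associated with improvements of the subjective prognosis of work ability and distress". The next sentence turns this into a directional hypothesis: "We assume that regular users have a more positive prognosis of work ability and less distress after participation", "compared to non-regular users, resp. drop-outs".
- **Statistical analysis:** "The differential efficiency of subjective prognosis of gainful employment and depression will be analysed with repeated measures ANOVA and regression analysis". The sentence does not name the groups between which efficiency differs. The utilisation contrast in the Objective is the natural referent, but that link is an inference.
- **Discussion:** the lack of a control group is called a possible limitation. Two replies follow. The first is to describe who is referred and accepts against who is not referred or refuses. The second, introduced as an addition, is to assess frequency and subjective evaluation of participation "in order to model treatment gains based on regular participation".
- **Participants and recruitment:** on recommending the programme, "This decision does not affect referrals for other aftercare programmes". Parallel aftercare is therefore possible.
- **Status:** the primary outcomes are the recommendation rate and participation. The Abstract calls the analysis of the secondary outcomes exploratory.

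**The concern.** How long someone keeps writing is settled after baseline and by the participant. Severity, motivation, expected return to work, parallel aftercare or early improvement can influence both continued use and the T1–T14 course of SPE and PHQ-9. A repeated measures ANOVA with two time points compares changes. It removes a stable difference in level at T1, but not a difference in natural course. It also cannot tell improvement caused by use from use caused by improvement.

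The first reply in the Discussion (referred and accepting patients against the others) deals with selection into the programme. Selection into continued use is not mentioned. A favourable contrast could therefore be reported as a gain from regular participation when the programme contributed none of it.

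A smaller mismatch sits beside this: the Objective speaks of distress, while the Statistical analysis section names depression.

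**Working it through.** **The plan's own figure.** N = 212 is a projection from clinic throughput and a 66% participation rate. Throughput is not given, so it cannot be reproduced; 212/0.66 would imply about 321 recommended patients. It is not a power calculation and serves here only as the sample size.

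**Inputs from the article.** N = 212; use in the earlier trial with mean 6.00 and SD 4.21 over 12 possible weeks; SPE and PHQ-9 measured at T1 and T14.

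**Assumed, not in the article.** No programme effect; correlation r between propensity to use and natural change of 0 to 0.3; regular use meaning at least 6 entries; two-sided 5% test; T14 response either complete, or 85% in regular and 45% in non-regular users.

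**Step 1, distribution of use.** A beta-binomial on 0–12 matched to the mean and SD has ρ = (4.21²/(12 × 0.25) − 1)/11 = 0.446 and a = b = (1/0.446 − 1)/2 = 0.62. P(use ≥ 6) = 0.058 + 0.059 + 0.061 + 0.064 + 0.071 + 0.084 + 0.132 = 0.529. This gives 212 × 0.529 = 112 regular and 100 non-regular users.

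**Step 2, apparent difference.** With change scaled to SD 1 and a normal propensity, the difference is r × φ(z)/(p(1 − p)). For p = 0.529, φ(z) = 0.398, so the factor is 0.398/(0.529 × 0.471) = 1.60. For r = 0.1, 0.2 and 0.3 the difference is 0.16, 0.32 and 0.48 SD.

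**Step 3, chance of significance.** With two time points, the group-by-time test equals a t-test on change scores.
- Full response: √(1/112 + 1/100) = 0.138. For r = 0.2 the within-group SD is √(1 − 0.2² × 1.597² × 0.529 × 0.471) = 0.987. Then 0.319/(0.987 × 0.1376) = 2.35, and Φ(2.35 − 1.96) = 0.65.
- 85%/45% response: 112 × 0.85 = 95 and 100 × 0.45 = 45, so √(1/95 + 1/45) = 0.181. Then 0.319/(0.987 × 0.181) = 1.79, and Φ(1.79 − 1.96) = 0.43.

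Simulation of the same set-up gives:

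| r | Apparent difference (SD) | Significant, full response | Significant, 85%/45% response |
|---|---|---|---|
| 0 | 0 | 5% | 5% |
| 0.1 | 0.16 | 21% | 14% |
| 0.2 | 0.32 | 65% | 42% |
| 0.3 | 0.48 | 94% | 77% |

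At r = 0, half of the 5% falls in the favourable direction. For negative r the table is mirrored: regular users appear worse by the same amounts. Response here depends only on user group, so it alters precision but not the difference.

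**Step 4, scale.** With 106 per group, 1.96 × √(2/106) = 0.27 SD already reaches p < 0.05. The article calls the effects in its earlier randomised trial small, without figures. This contrast could not separate an effect of that order from a purely confounded difference.

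**The case against.** Much can be said for the plan. The Objective already speaks of association and of different levels of utilisation, and the Statistical analysis section names regression beside ANOVA. A graded analysis is therefore compatible with the text, and a two-group split need not be the only one. Efficacy was the subject of the earlier randomised trial; here it is a secondary question. All of this stands and limits the weight of the point. It does not cover the Discussion, which goes from association to treatment gains without naming self-selection.

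Some stronger readings are tempting but unsupported:
- **The cut-off for regular use is open to choice after the data are seen, and confounders are ignored.** The article gives neither a cut-off nor covariates, but such details may sit in a full protocol or analysis plan that is not shown. Their absence from an article is not an error, and nothing suggests a data-driven cut.
- **The distress hypothesis is not tested.** PSS-4 and PHQ-stress remain listed secondary outcomes, and depression can fall under distress. Only the labels are loose.
- **The contrast replaces the control group.** It is the second of two replies and is offered as an addition.

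The size and sign of r are also assumptions. Early improvers may stop writing and more burdened patients may continue, which would work against regular use.

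**Conclusion.** The concern holds as a matter of interpretation and choice of main analysis. The contrast between self-selected regular and non-regular users cannot carry a statement about treatment gains, and the planned T1/T14 ANOVA does not change that. Under the assumptions above, a programme without effect would show regular users 0 to 0.48 SD better for r from 0 to 0.3. The result would be significant in 5 to 94% of trials with full T14 response, or 5 to 77% with the lower response.

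A reader might infer that a spurious benefit is likely in this trial. The documents do not support that: they give no value for r, at r = 0 there is no inflation, and a negative r reverses the bias. What can be said is that a modest shared cause is enough to produce a clear result in either direction. The primary outcomes are untouched, so severity is low to moderate.

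**What to change.** - **Statistical analysis:** make the main utilisation analysis a regression of T14 SPE, and separately of T14 PHQ-9, on the number of weekly diary entries (0–12) as a continuous term. Adjust for the T1 value and clinic or indication. Where the clinic data can be linked to the pseudonymous questionnaires, also adjust for age, sex, functioning at discharge and other recommended aftercare. Use any regular/non-regular split descriptively only. State the source of the count: entries are written on the web application, but the article also has utilisation asked at T14.
- **Statistical analysis and Discussion:** replace *differential efficiency* and *treatment gains* with *association*, in line with the Objective, and name self-selection into continued use as a limitation.
- **Objective and Statistical analysis:** align distress with depression, either by saying that PHQ-9 carries the hypothesis or by naming the stress scale that does.

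**Cost:** mostly wording, with no new assessments. Linkage is not described in the article and must be confirmed before the clinic covariates are promised. The claim becomes more modest, and residual confounding remains: baseline covariates cannot capture improvement that occurs after T1, and clinic records show which other aftercare was recommended and accepted, not what was used.

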### Outcomes

#### Primary outcomes

Recommendation rate of *‘GSA-Online plus’*. How often will *‘GSA-Online plus’* be recommended as an aftercare after inpatient rehabilitation?Number of patients participating in *‘GSA-Online plus’*. At least 66% of patients with a corresponding recommendation should use *‘GSA-Online plus’* at least once.

### Secondary outcomes

All of the following secondary outcomes are assessed at T1 (study inclusion) and T14 (12 weeks later):Subjective Prognosis of Gainful Employment (SPE)Work ability (WAI)Depression (PHQ-9)Anxiety (GAD-7)Somatic symptoms (SSS-8)Overall health status (EQ-5D-3 L)Psychosocial stressors (PHQ-Stress)Psychological stress (PSS-4)General functioning (Sheehan-Disability Scale)Loneliness (LS-S)Personal resources (OSS-3 and BRCS)

The following secondary outcomes are only assessed at T14 (12 weeks after study inclusion):Overall satisfaction (modified version of ZUF-8) with *‘GSA-Online plus’* as well as helpfulness and utilizationEvaluation and utilization of the video clipsWillingness to pay and amount of payment for *‘GSA-Online plus’*

A weekly regular monitoring takes place at T2 till T13 (12 weeks during intervention):Self-rated health status (Item drawn from the EQ-5D)Self-rated work ability (Item drawn from the WAI)Satisfaction and helpfulness of the therapeutic feedback

### Sample size

Utilization of *‘GSA-Online plus’* will be examined under conditions of usual care. We will assess how often *‘GSA-Online plus’* will be recommended as an aftercare after inpatient rehabilitation compared to normal aftercare programmes. Therefore, no sample size will be defined. During the period of recruitment all rehabilitants will be included, who obtain an aftercare recommendation of *‘GSA Online plus’* and have the intention to participate. On the basis of the official statistics of the number of treated rehabilitants in the participating clinics and a participation rate of 66% in our prior study we anticipate *N* = 212 participants in all three clinics over a period of 9 months.

### Statistical analysis

Frequencies and descriptive statistics will be used to evaluate recommendation rate and utilization of *‘GSA-Online plus’*. The differential efficiency of subjective prognosis of gainful employment and depression will be analysed with repeated measures ANOVA and regression analysis. Willingness to pay and the utilization criteria of online aftercare will be reported with frequencies and descriptive statistics.

## Discussion

While internet-based interventions have been demonstrated to be efficacious, drawbacks refer to participation and implementation into clinical practice. In clinical practice, participation rates and compliance have been found to be less than satisfactory [42]. Thus, most programmes have not found a place in usual care. Dissemination and implementation of efficacious, evidence-based treatments into medical practice has become a growing issue for mental health care [43]. Therefore it is important to investigate how interventions evaluated in RCTs with selected participants, usually recruited over the internet, can be transferred into routine clinical care, and whether the health care system benefits from such developments. Thus, we implemented a transdiagnostic programme found efficacious in a previous RCT [25] into clinical practice. However, in order to be successfully implemented in routine clinical care, an online intervention needs to be self-explanatory, i.e. easy to handle by busy and changing staff members. Therefore, we augmented the programme by additional exploratory and motivational videos on the study web application to familiarize potential participants and medical professionals with the internet-based aftercare programme. Based on our previous experience with a considerable number of drop-outs from the programme we also took care to motivate them to follow through with it [26]. As other aftercare interventions, referrals to *‘GSA-Online plus’* are made by the physicians in charge. The focus of evaluation is on acceptance of the programme, both by the physicians in charge and the patients. The lack of a control group may be seen as a limitation. However, we take care to specify who gets referred, respectively accepts the recommendation compared to those who do not get the recommendation, respectively refuse to participate. Additionally, we assess the frequency and subjective evaluation of participation in order to model treatment gains based on regular participation. If our implementation study proves to be successful, a next step will be to resolve legal requirements and financial resources necessary to implement *‘GSA-Online plus’* as a regular aftercare programme for vocationally stressed inpatients of medical rehabilitation.

## Abbreviations

BRCS: Brief Resilient Coping Scale
CCRT: Core Conflict Relationship Theme
EQ-5D-3 L: EuroQol
GAD-7: General Anxiety Disorder Scale
GSA-Online plus: Gesund und Stressfrei am Arbeitsplatz [Healthy and Without Stress at the Workplace]- Online plus
GSA-Online: Gesundheitstraining Stressbewältigung am Arbeitsplatz [Health Training Stress Management at the Workplace]- Online
LS-S: Loneliness Scale
OSS-3: Oslo Support Scale
PHQ: Patient Health Questionnaire
PSS-4: Perceived Stress Scale (short-form)
RCT: Randomised controled trial
SET: Supportive expressive therapy
SPE: Subjective Prognosis of Work Ability Scale
SSS-8: Somatic Symptom Scale
WAI: Work Ability Index
ZUF-8: Fragebogen zur Messung der Patientenzufriedenheit [CSQ-8: Client Satisfaction Questionnaire]
